### Treatments

(a) The Bacopa supplement used in ARCLI is an extract of *Bacopa *monnieri called CDRI08 and is commercially available as KeenMind™ (Flordis). This product is manufactured from the stems, leaves and roots of *Bacopa *and is extracted with 50% ethanol. It is standardized to contain active bacosides at levels of 55% ± 5%. This extract has previously been shown to enhance cognitive performance at this dosage after 3 months of supplementation [44,45].

(b) Pycnogenol (Horphag Research, Geneva, Switzerland) is a patent extract made exclusively from the bark of French maritime pine trees (*Pinus pinaster*). Pycnogenol contains consistent proportions of bioflavonoids and is standardized to contain 70 ± 5% procyanidins. This dosage of Pycnogenol has previously been shown to enhance memory performance after 3 months of supplementation [42].

### Randomization and safety

An independent researcher (Medical practitioner) located at an independent university will be responsible for the randomization of the study treatments and will chair the safety committee. Participants will be randomly assigned to one of the three treatment groups according to a Latin square design. Randomization codes will be kept in a sealed opaque envelope in a secure safe and will only be opened in case of emergency.

### Primary outcome

The primary study outcome is the effect of supplementation on cognitive performance as measured by a battery of well validated and highly sensitive cognitive tests. These tests will be implemented at baseline and all follow-up time points (3, 6 and 12 months post baseline). This battery will include all tasks from the Cognitive Drug Research (CDR) Computerized Assessment System and selected tasks from the Swinburne University Computerized Cognitive Assessment Battery (SUCCAB). Table 1 lists the cognitive measures assessed by the CDR and SUCCAB batteries. Wechsler intelligence (Wechsler Abbreviated Scale of Inteligence-WASI) will also be administered as both an estimate of pre-morbid intelligence as well as a factor to determine whether IQ predicts response to any of the supplements.

**Table 1 T1:** Cognitive domains measured by CDR and SUCCAB tests

CDR	SUCCAB	Hick RT	Inspection Time
Simple RT	Stroop Colour-Word	Simple Decision Time	Perceptual Speed
Choice RT	Spatial Working Memory	Simple Movement Time	
Spatial WM	Contextual Memory	2 Choice Decision Time	
Numeric WM	Immediate/Delayed Recognition	2 Choice Movement Time	
Picture Presentation		4 Choice Decision Time	
Immediate Word Recall		4 Choice Movement Time	
Digit Vigilance		8 Choice Decision Time	
Delayed Word Recall		8 Choice Movement Time	
Word Recognition			
Picture Recognition			
Rapid Visual Information Processing			

CDR = Cognitive Drug Research, SUCCAB = Swinburne University Computerized Cognitive Assessment Battery, RT = Reaction Time, WM = Working Memory

The CDR battery has been used in well over 1000 clinical trials world wide, is well validated, and has been shown to be sensitive to the effects of several natural supplements including Bacopa and Pycnogenol [42,44]. The SUCCAB is sensitive to the effects of age-associated cognitive decline and has been recommended for use when assesing cognitive changes following nutraceutical supplementation [46]. The SUCCAB has also been shown sensitive to the effects of a pine bark extract similar to Pycnogenol [47]. Both the CDR and SUCCAB provide detailed assessments of memory performance (both short and long term), a domain of cognition expected to be modulated by treatment. The cognitive demand battery [48] will be implemented to assess the effects of supplementation on cognitive effort and fatigue whilst the MMSE [49] will be used as a dementia screening tool at intake and to monitor the effects of treatment on global cognitive decline (after randomization). The Inspection Time task [50] and Hick Reaction Time paradigm [51] will be used as they provide highly valid and sensitive assessment of mental speed which has been shown to slow with increasing age.

### Secondary outcomes

A wide range of psychological, cardiovascular, biochemical and genetic measures will also be collected at different time points as part of ARCLI. These are described below and listed in Table 2.

**Table 2 T2:** Summary of the secondary outcomes implemented in ARCLI across all time points

	Training	Baseline	3 month	6 month	12 month
**Screening**	Medical history & screen (GDS, MMSE, DRS-II) Demographic Q	Medical screen (ie BMI, MMSE, medication use)	Medical screen (ie BMI, MMSE, medication use)	Medical screen (ie BMI, MMSE, medication use)	Medical screen (ie BMI, MMSE, medication use)
**Biochemical**	Fasting Glucose & Insulin* APOE & SNP	F2 Isoprostanes Cytokines* & CRP MBA Telomere length	F2 isoprostanes Cytokines* & CRP MBA	-	F2 isoprostanes Cytokines* & CRP MBA Telomere length
**Cardiovascular**	-	Brachial BP Aortic BP carotid-femoral PWV	Brachial BP Aortic BP carotid-femoral PWV	Brachial BP Aortic BP carotid-femoral PWV	Brachial BP Aortic BP carotid-femoral PWV
**Health**	FFQ Chalder Fatigue Leeds Sleep evaluation Trait anxiety	General Health Q State anxiety Leeds Sleep Evaluation BDI-II POMS	General Health Q State anxiety Leeds Sleep Evaluation BDI-II	General Health Q State anxiety Leeds Sleep Evaluation BDI-II	FFQ General Health Q State anxiety Leeds Sleep Evaluation BDI-II
**Other**	NEO PI-R WASI				Estimate of compliance

* = Analysis performed for morning participants only

GDS = Geriatric Depression Scale, MMSE = Mini Mental State Examination, DRS = Mattis Dementia Rating Scale, Q = Questionnaire, APOE = Apolipoprotein E, SNP = Single Nucleotide Polymorphisms, WASI = *Wechsler Abbreviated Scale of Intelligence *FFQ = Food Frequency Questionnaire, NEO PI-R = NEO Personality-Inventory Revised, POMS = Profile of Mood States, BMI = Body Mass Index, CRP = C Reactive Protein, MBA = Multiple Blood Analysis, BP = Blood Pressure, PWV = Pulse Wave Velocity

### Mood, health and dietary habits

Numerous self-report questionnaires will be used to assess mood and general health. Depressive symptoms and state-trait anxiety will be measured with the Beck Depression Inventory II (BDI-II) [52] and the Spielberger State-Trait Anxiety Inventory [53] respectively. Further assessment of mood will be performed with the Profile of Mood Scales [54] and the Bond and Lader Visual Analogue Scales [55]. Throughout the trial, general health, fatigue and sleep quality will be assessed with the General Health Questionnaire [56], Chalder Fatigue Scale [57] and the Leeds Sleep Evaluation Questionnaire [58] respectively. Dietary habits will be inferred from an in-house Food Frequency Questionnaire.

### Cardiovascular

Brachial pressures, aortic pressures and carotid-femoral Pulse Wave Velocity (PWV) are not only associated with cardiovascular disease risk and mortality [59,60] but also cognitive performance and decline [61,62]. These variables can all be modified by diet and lifestyle changes [63-65] and will therefore be monitored throughout the trial as one possible mechanism by which the study supplements improve brain function. Brachial blood pressure will be measured after a 5 minute rest period using a clinically validated automated sphygmomanometer. Applanation tonometry of the radial artery will be used to estimate aortic pressures and wave reflections using a non-invasive SphygmoCor device. The same SphygmoCor device will be used to measure PWV through applanation of the carotid and femoral arteries. In addition to this assessment, cerebral and common carotid blood flow velocity and endothelial dependent vasodilation of the brachial artery may be measured on a subset of participants using transcranial Doppler and flow mediated dilation respectively.

### Biochemical

Pre-randomization, one off biochemical assessment will be conducted to measure glycated haemoglobin (HbA1c) and insulin levels. Measurement of blood glucose and insulin will provide a measure of baseline glucoregulatory efficiency and control, which may contribute to age-related cognitive decline [66]. At both baseline and selected follow-up time points, biochemical markers of oxidative stress, inflammation and safety profiling will be measured through high sensitivity C-Reactive Protein, F2-Isoprostanes, inflammatory cytokines (e.g. TNF-α, IL-2, IL-4, IL-6, IL-10 & IFN-gamma) and Liver Function Tests.

### Genetic

Blood collected pre-randomization will also be used to assess a platform of Single Nucleotide Polymorphisms thought to be related to cognitive/brain function, general health or response to treatment. This will include assessment of the APOE4 allele, which is associated with an increased risk of AD [67] and cognitive decline in normal elderly [68] but also more than 100 targeted polymorphisms including BDNF, cytokines amongst others. Genotyping will allow investigation of whether certain polymorphisms affect response to treatment or show differential relationships with the cognitive and biological variables. Telomere length (a marker of genetic damage) will also be assessed at baseline and 12 months to investigate whether any of the treatments modulate telomere shortening over the duration of the study.

### Analysis

The primary analysis will investigate the effects of treatment on all cognitive outcomes over the course of the study using Analysis of Variance (ANOVA) techniques. Other more powerful statistical techniques such as linear mixed modelling and intention to treat analysis will be considered. Similar statistical techniques will be used to investigate the effects of treatment on the secondary outcomes. Pearson's correlation coefficients will be used to investigate whether any improvements in cognition are related to improvements in other variables of interest such as biochemical, cardiovascular or mood/health factors. Correlations and regression models may be used to examine baseline associations between variables. Results will be considered statistically significant at p < 0.05 corrected for multiple cognitive factors (primary outcome variables) or p < .05 for secondary outcome variables.

Covariates such as age, gender and baseline cognitive screening measures (e.g., MMSE and Wechsler intelligence) will be adjusted for in the analyses. Results will be presented as appropriate effect sizes with a measure of precision (95% confidence intervals). Compliance to treatment will be analysed by counting each participants remaining supplements once they have completed the trial.

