### Procedure

Eligible participants are required to attend five testing session. An overview of the testing sessions is provided in the clinical trial flow chart (Figure 1). During the first session, participants are screened for eligibility and a detailed history is taken. Eligible participants are then asked to give blood and to complete the cognitive test batteries multiple times. This allows the participant to familiarize themselves with the cognitive tasks and minimises practice effects (as well as establishing that the participant lies within established norms for their age group). Cognitive data obtained during the training visit will not be included in statistical analysis. Visit 2 involves baseline assessment of all measures and randomization to treatment. Participants are to commence taking their assigned treatment on the day following their baseline assessment. As depicted in Figure 1, visits 3 to 5 involve follow-up assessment at 3, 6 and 12 months post randomization. At the 12 month assessment, participants will be asked to return any remaining supplements, such that they can be counted enabling the investigators to estimate compliance to treatment.

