### Sample size

The sample size for this study is 465 participants with 155 participants in each arm. Previous studies using Bacopa and Pycnogenol have reported statistical significance on measures of cognition with approximately 100 participants in each of these studies respectively [42,44]. Based on these previous studies, the current sample size of 465 ensures adequate power to detect a significant effect 80% of the time when conducting two-tailed tests using 95% confidence even when allowing for a 10-20% attrition rate.

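### ANOVA is named as the primary analysis while the mixed model and intention to treat are only to be considered, in a trial that allows for 10-20% attrition

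*Protocol article*

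**What the plan says.** All references are to the protocol article.

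- **Analysis**, on the primary method: "The primary analysis will investigate the effects of treatment on all cognitive outcomes over the course of the study using Analysis of Variance (ANOVA) techniques".
- **Analysis**, next sentence: "Other more powerful statistical techniques such as linear mixed modelling and intention to treat analysis will be considered".
- **Sample size**: "The sample size for this study is 465 participants with 155 participants in each arm". This number is said to give 80% power "even when allowing for a 10-20% attrition rate".
- **Procedure** and **Primary outcome**: cognition is assessed at baseline and at 3, 6 and 12 months, so each person has one baseline and three follow-up measurements.
- **Analysis**, on compliance: "Compliance to treatment will be analysed by counting each participants remaining supplements once they have completed the trial". **Procedure** agrees: "At the 12 month assessment, participants will be asked to return any remaining supplements". Table 2 lists the compliance estimate in the 12-month column only.

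The article nowhere commits to analysing participants in the arm to which they were randomised. Attrition appears only as a matter of power.

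**The concern.** This is a stated rule, not a gap left for a later document. The article ranks ANOVA first and makes analysis as randomised optional. It also lists intention to treat among more powerful techniques, although it is a choice of who is analysed and in which arm, not a technique. The mixed model is described as better than the chosen method and yet is not adopted.

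What is at stake is mainly bias. If people who do not improve leave more often, and this differs between a supplement and placebo, comparing those who remain no longer compares the randomised groups. A mixed model uses the visits that early leavers did attend and is valid under a weaker assumption, missing at random given the observed data. Complete-case ANOVA discards that information.

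Compliance is a smaller, separate matter. On the text, nobody who withdraws before 12 months has leftover supplements counted, so the reported compliance describes completers.

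**Working it through.** **1. The plan's own figure.** 3 x 155 = 465, which agrees. The 80% power claim cannot be reproduced because no effect size or SD is given. The standardised difference detectable with 80% power at two-sided 5% can be derived instead, assuming a two-arm comparison with no gain from baseline adjustment: d = (1.960 + 0.842) x sqrt(2/n).

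| Attrition | People lost | n per arm | Detectable d |
|---|---|---|---|
| 0% | 0 | 155 | 0.318 |
| 10% | 46.5 | 139.5 | 0.335 |
| 20% | 93 | 124 | 0.356 |

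The cost in power is small.

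**2. Who would be excluded.** This depends on the form of ANOVA, which is not stated.
- Repeated-measures ANOVA with listwise deletion excludes anyone missing any visit. If visits were missed independently at 3% or 5% each (assumed), three follow-ups would exclude 1 - 0.97^3 = 8.7% or 1 - 0.95^3 = 14.3%, even without permanent dropout.
- ANOVA at a single visit excludes only those absent then. At 12 months that still leaves out everyone who has withdrawn and is not assessed.

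**3. Bias by simple algebra.** If a fraction p of an arm drops out and dropouts are g SD worse than completers, the completers' mean exceeds the arm's true mean by p x g. With the same g in both arms, the bias is (p_active - p_placebo) x g. The widest split inside the planned range is 20% against 10%:
- g = 0.3: 0.10 x 0.3 = 0.03 SD
- g = 0.5: 0.10 x 0.5 = 0.05 SD
- g = 1.0: 0.10 x 1.0 = 0.10 SD

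With 20% in both arms and the same g, the bias is 0.

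**4. Bias by simulation.** Common settings: 155 per arm, correlation 0.7 between visits, no true effect, completers-only comparison, 3,000 or 4,000 trials per setting. All dropout mechanisms are assumed. In the rows with one mechanism in both arms, dropout follows a logistic model on the last observed change, with slope 1 per SD.

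| Dropout, active / placebo | Mechanism | Bias (SD) | Type I error |
|---|---|---|---|
| 20% / 20% | same in both arms | 0.00 | 4.9% |
| 22% / 17% | same in both arms | +0.02 | 5.4% |
| 20% / 10% | same in both arms | +0.035 | 6.4% |
| about 21% / 17% | active only, moderate dependence | +0.04 | 7.0% |
| about 21% / 17% | active only, stronger dependence | +0.06 | 10.2% |
| 22% / 17% | active only | +0.07 | 10.8% |
| 22% / 17% | active only, slope 1 per SD | +0.08 | 13.6% |

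A further run gave 0.00 to +0.03 SD and about 5-6.5% with a shared mechanism, and +0.06 SD and about 9-10% with the active-only mechanism. In the fourth to sixth rows' settings, an estimate that uses the observed visits under missing at random was unbiased to within 0.003 SD. That result is expected, because dropout was generated as missing at random.

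**5. Scale.** Against the detectable 0.356 SD at 20% loss, 0.03 SD is 0.03/0.356 = 8%, and 0.08 SD is 0.08/0.356 = 22%.

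**The case against.** The strongest reply has four parts.

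- **The article never says completers only, or even repeated-measures.** That is correct. A reader might infer that 10-20% of participants will be removed from the primary result. The text does not support this: the percentage is a planning allowance, and per-visit ANOVA with covariates also fits the wording. The exclusion is conditional on the form of ANOVA.
- **The larger error rates come from giving the arms different dropout mechanisms.** This also stands. Nothing in the documents indicates such an asymmetry in a double-blind trial, and 22% lies just outside the planned range. With one mechanism in both arms, type I error stays near 5-6.5%. Reading a type I error above 10% as the expected result, or the randomised comparison as lost, is not supported.
- **Compliance does not define the analysis set.** Agreed. A reader might link the completers' supplement count to the loss of people from the efficacy result, but no section makes that link.
- **A fuller protocol or analysis plan may settle the model.** It may, so the article does not show that the choice will be made after seeing data. But the reply does not remove the point: the article itself fixes ANOVA as primary and leaves analysis as randomised undecided. Any later plan would have to depart from it.

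The mixed model is no complete cure either. If dropout depends on unobserved outcomes, it can be biased too.

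**Conclusion.** The point holds in a limited form. The article positively names ANOVA as primary and leaves both the mixed model and intention to treat open, while allowing for the loss of about 47 to 93 of 465 people. The possible bias runs from about 0.00 to +0.03 SD under a shared outcome-dependent mechanism to about +0.06 to +0.08 SD when only the active arms' dropout depends strongly on outcome; a moderate dependence gave +0.04 SD. These figures rest on assumed dropout mechanisms, a visit correlation of 0.7 and a completers-only analysis. They show what the open wording permits, not what will happen. The commitment is worth making because it costs almost nothing and protects the randomised comparison. The compliance gap is real but minor, and it stands apart from the efficacy analysis.

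**What to change.** 1. State one primary analysis: a linear mixed model for repeated measures with all randomised participants in their assigned arm, visit and arm-by-visit terms, and the 12-month contrast of each supplement with placebo.
2. Say how people with no follow-up are handled, for example by keeping baseline as an outcome in the model. Restricting to those with any follow-up would not be full intention to treat, because it omits anyone who leaves before month 3.
3. Make the complete-case ANOVA a sensitivity analysis, and add one sensitivity analysis under a missing-not-at-random assumption.
4. Separately, count returned supplements at withdrawal and at the existing 3- and 6-month visits as well as at 12 months. Do not use the count to define the efficacy analysis set.

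Items 1 to 3 cost a few sentences and some extra analysis code. Item 4 adds a supplement count at visits that already take place, and a request to return supplements on withdrawal.

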### Participants

A total of 465 healthy, elderly participants aged between 60 and 75 years will take part in the study. This restricted age range was chosen due to the large variation in cognitive abilities and trajectories associated with ageing. Participants will be randomized to receive one of three daily treatments for 12 months: ***(a) ***300 mg *Bacopa *(KeenMind CDRI 08 extract); ***(b) ***150 mg Pycnogenol; or (c) placebo. Participants will be excluded from participation if they are a current smoker; have a psychiatric or neurological disease; significant endocrine, gastrointestinal or cardiovascular disorder; other disorder affecting food metabolism; recent history (past 5 years) of chronic/severe illness (longer than 6 weeks); current regular alcohol use exceeding 14 standard drinks per week for women and 28 standard drinks per week for men; vision that is not corrected to normal. To be eligible, participants cannot be taking psychoactive medication including, antidepressants, antipsychotics, anxiolytics, cholinesterase inhibitors, illicit drugs or significant cognitive enhancing drugs (e.g. chronic intake of substances such as Ginkgo). Participants who are irregular users of vitamin or herbal supplements will be asked to stop taking them for the duration of the trial. Participants who are regular users (defined as daily intake for greater than 3 months) of vitamins or herbal supplements will be asked to maintain the same habits throughout the trial. Participants with either global cognitive impairment or significant levels of depressive symptoms, as determined by a score < 24 on the Mini Mental State Examination (MMSE) or a score > 19 on the Geriatric Depression Scale respectively, will be excluded. To ensure that participants do not have probable dementia, those scoring between 24-26 on the MMSE will be administered the Dementia Rating Scale II (DRS-II). Any questionable cases on the DRS-II will be discussed by the ARCLI participant safety committee for agreement on eligibility. The study was ethically approved by the Swinburne University Human Research Ethics Committee (project number 2010/106) and all participants will provide written informed consent. The trial has been registered with the Australian and New Zealand Clinical Trials Registry (ACTRN12611000487910).

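### The named covariates do not include each test's own visit 2 score, and the text does not say how baseline enters the ANOVA, so available precision is not secured

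*Protocol article*

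**What the plan says.** The Analysis section of the protocol article sets the primary analysis as the "effects of treatment on all cognitive outcomes over the course of the study using Analysis of Variance (ANOVA) techniques". It adds: "Other more powerful statistical techniques such as linear mixed modelling and intention to treat analysis will be considered". On adjustment it says: "Covariates such as age, gender and baseline cognitive screening measures (e.g., MMSE and Wechsler intelligence) will be adjusted for in the analyses".

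The own baseline score is available. The Procedure section states: "Visit 2 involves baseline assessment of all measures and randomization to treatment". The Primary outcome section confirms that the cognitive tests are given at baseline and again at 3, 6 and 12 months. The Procedure section also says: "Cognitive data obtained during the training visit will not be included in statistical analysis". That sentence concerns visit 1 and does not bar use of the visit 2 scores.

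Two things are not stated: whether the visit 2 score of the test under analysis is a covariate, and whether baseline is a level of the time factor, a covariate, or outside the model.

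**The concern.** When the same test is given before and after randomization, its own baseline is usually the strongest single predictor of the follow-up score. The Analysis section does name baseline cognitive information to adjust for, but the class it names is screening measures, with MMSE and Wechsler IQ as examples. The CDR, SUCCAB, Hick and Inspection Time scores are outcomes, and their own baselines are not mentioned.

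The named measures are weaker stand-ins. MMSE is cut off below 24 by the eligibility rule in the Participants section, so its range is narrow. Wechsler IQ does not have that limit, but it is a general measure taken once, at the training visit (Table 2).

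At stake are the width of the confidence intervals and the power of each comparison with placebo. Protection against chance imbalance in the score being analysed is also at stake. Precision matters more here because the primary tests are to be corrected for multiple cognitive factors, so each runs at a stricter level than 5%.

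**Working it through.** **The plan's own figure.** The Sample size section says: "The sample size for this study is 465 participants with 155 participants in each arm". The arithmetic agrees: 3 × 155 = 465. The number itself cannot be re-derived, because no effect size or SD is given. It can be inverted: detectable difference in SD units = √(2/n) × (1.960 + 0.842), for two-sided 5% and 80% power on a follow-up score alone.

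- No attrition, n = 155: 0.318
- 10% attrition, n = 139.5: 0.336
- 20% attrition, n = 155 × 0.8 = 124: 0.356

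**Inputs for the comparison.**

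- n = 124 per arm: the document's figure at its upper attrition rate.
- Difference d = 0.30 SD: assumed.
- Correlation r between baseline and follow-up = 0.6 to 0.8: assumed.
- Equal variances at each visit, two-sided 5% without multiplicity correction. The absolute powers are therefore optimistic.

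**Variance at one follow-up visit, relative to the follow-up score alone.**

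- Follow-up only: 1
- Change from baseline (what a group by time contrast amounts to if baseline is a level of time): 2(1 − r)
- Covariance analysis on own baseline: 1 − r²
- Ratio of change to covariance analysis: 2/(1 + r)

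Power is approximately Φ(d/√(2V/n) − 1.960), where V is the relative variance.

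| r | V change | V own baseline | Ratio | Power, follow-up only | Power, change | Power, own baseline |
|---|---|---|---|---|---|---|
| 0.6 | 0.80 | 0.64 | 1.25 | 66% | 75% | 84% |
| 0.7 | 0.60 | 0.51 | 1.18 | 66% | 86% | 91% |
| 0.8 | 0.40 | 0.36 | 1.11 | 66% | 96% | 98% |

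Worked line for r = 0.7:

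- Change: standard error √(2 × 0.60/124) = 0.0984; 0.30/0.0984 = 3.05; power 86%.
- Own baseline: standard error √(2 × 0.51/124) = 0.0907; 0.30/0.0907 = 3.31; power 91%.

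**Mean of the three follow-ups instead of one visit.** Take equal correlation 0.7 between all visits and the same d at each. The mean follow-up has variance (1 + 2 × 0.7)/3 = 0.80. The contrast with baseline has 0.80 + 1 − 1.4 = 0.40, power 96%. Covariance analysis has 0.80 − 0.49 = 0.31, power 99%. The gain is about 3 points.

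**How much the named covariates recover.** Suppose they correlate q with both the baseline and the follow-up score (q = 0.3 to 0.5, assumed).

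- A follow-up-only analysis adjusted for them has residual variance 1 − q² = 0.91 to 0.75.
- Adding the own baseline uses the partial correlation (r − q²)/(1 − q²). At r = 0.7 this is 0.67 for q = 0.3 and 0.60 for q = 0.5. Residual variance becomes 0.91 × (1 − 0.67²) = 0.50 and 0.75 × (1 − 0.60²) = 0.48.
- For a change contrast, such covariates recover nothing: (1 − q²) × 2 × (1 − partial correlation) = 2(1 − r).

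So the named covariates do part of the work in a follow-up-only analysis, and under this assumption none in a change-type analysis.

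**The case against.** The strongest reply is that nothing in the text excludes baseline adjustment. The list is introduced with such as and uses e.g., so it is illustrative, and an analysis plan that is not shown may complete it. This stands, and it is why the point is that precision is not secured, rather than that it is lost. It does not remove the point. The article chose to name its baseline cognitive covariates and named a weaker class than the one it collects, and adding the own baseline costs nothing.

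The second reply is that an ANOVA over the course of the study may already use baseline as a repeated level, so that group by time contrasts keep most of the information and offset chance imbalance. This also stands in part: at a correlation of 0.8 the remaining gain is between 1 and 2 power points.

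Two stronger readings are tempting and are not supported.

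- A reader might infer that baseline will be a level of time and that treatment will be tested by a group main effect averaged over it, diluting the effect with a visit where none can exist. The text never says so. The Aims and study hypotheses section speaks of improvement relative to placebo at each time point, which points to group by time or per-visit contrasts.
- A reader might infer bias. Under randomization, follow-up-only, change-type and baseline-adjusted analyses all estimate the same effect without bias. They differ in precision and in how they treat chance imbalance.

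**Conclusion.** The point holds as one of efficiency and clarity. The article names age, gender and screening measures as example covariates, leaves the own visit 2 score unnamed, and does not say how baseline enters the ANOVA.

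In large samples, covariance analysis on the own baseline is never less precise than the change-type or follow-up-only alternatives. Over a change-type contrast, the gain is 20% down to 10% of the variance, or about 9 down to 1 power points, as the assumed correlation goes from 0.6 to 0.8. Over a follow-up-only analysis with no covariates it is 36% to 64% of the variance. The screening measures would recover some of that.

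These sizes rest on an assumed difference of 0.30 SD and on assumed correlations; the document gives neither. The direction does not depend on them.

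**What to change.** Add one sentence to the analysis section: each cognitive outcome, and each secondary outcome measured at visit 2 and again later, is analysed at follow-up with its own visit 2 score as a covariate, alongside the covariates already named. In a repeated-measures or mixed model, the baseline score should also interact with visit. State too that baseline is not averaged into the treatment effect as a level of time.

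The cost is that sentence. The scores are already collected, and the sample size, visits and procedures stay as they are. It should be fixed before unblinding.
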